## Abstract

**Introduction::**

Chemotherapy regimens are often a 2-drug regimen in concurrent chemotherapy and radiotherapy for esophageal cancer (EC). However, some retrospective studies have suggested that for patients with EC receiving radiotherapy combined with 2-drug chemotherapy have the severe toxicity. And S-1 alone with the combination of radiotherapy treatment effect is good, and achieved good clinical remission rate. The purpose of this trial is compare the efficacy and toxicity of combining S-1 or S-1 plus cisplatin with radiotherapy for esophageal squamous cell carcinoma.

**Methods/Design::**

The study is a randomized, controlled, multicenter trial, comparing S-1 versus S-1 plus cisplatin concurrent radiotherapy for patients with esophageal squamous cell carcinoma. Eighty-eight patients with unresectable or medically unfit for surgery esophageal squamous cell carcinoma (clinical stage I to III), will randomly assigned to receive four cycles (2 concomitant and 2 postradiotherapy) S-1 or S-1 plus cisplatin along with radiotherapy 60–66 Gy/30 to 33 fractions. The primary outcome is complete response rate of primary tumor which will be measured by endoscopy and computer screen at 3 months after the completion of treatment. Secondary outcomes include survival and toxicity.

**Discussion::**

To our knowledge, this study protocol is the first to test the effect between S-1 versus S-1 plus cisplatin concurrent intensity modulated radiation therapy in the treatment of esophageal squamous cell carcinoma. If the result will be the same effect and fewer side effects and less costly in S-1 plus radiotherapy. It will supply more treatment selection for esophageal squamous cell carcinoma.

## Introduction

1

Esophageal cancer (EC) is a common malignancy worldwide.^[1]^ Squamous cell carcinoma is the most common histological type of EC worldwide, with a higher incidence in developing nations.^[2]^ In China, in 2015, the total incidence and mortality rates of EC were 477.9 and 375.0 per 100,000 persons, respectively, and over 90% of cases are esophageal squamous cell carcinoma.^[3,4]^ The incidence and mortality of EC ranks third in China. Yanting in Mianyang city is one of the highest risk areas for EC in the world.^[5]^

Surgery, radiation therapy, and chemotherapy are the major treatments for EC. But at initial diagnosis, 40% to 60% of patients are not candidates for surgery.^[6]^ In these patients, definitive chemoradiotherapy (CRT) is the established treatment of choice. Early trials have shown beneficial effects of CRT compared to radiotherapy alone,^[7,8]^ and definite CRT has been shown in smaller studies to be comparable in efficacy to surgery in patients with nonmetastatic disease.^[9,10]^ Concomitant use of chemotherapy and a radiation dose schedule that is more efficient compared to conventional radiotherapy may provide better outcomes in patients with EC.^[11]^ The chemotherapeutic drugs cisplatin and 5-fluorouracil have been most commonly used in studies examining the effects of definitive CRT in EC.^[12]^ However, despite many advances in diagnosis and treatment, the 5-year survival rate for patients diagnosed with EC ranges from 15% to 20%.^[12]^

Chemotherapy regimens are often a 2-drug regimen in concurrent chemotherapy and radiotherapy for EC.^[13]^ However, some retrospective studies have suggested that for patients with EC receiving radiotherapy combined with 5-FU/cisplatin chemotherapy, due to severe toxicity, only 9% to 38.5% of patients completed the planned treatment. In addition, one study showed that patients receiving radiotherapy combined with 5-FU/CDDP chemotherapy experienced a treatment-related mortality as high as 18%.^[7,14–17]^ Therefore, it is necessary to explore the toxicity of the combined program to improve its treatment tolerance and safety.

In recent years, S-1 reflects the good effect, single use or combined with platinum or combined with radiotherapy have achieved good results, especially the S-1 alone with the combination of radiotherapy treatment effect is very good, and achieved good clinical remission rate (CR).^[18–22]^

Therefore, we designed a prospective, randomized, multicenter phase II trial to compare the efficacy and toxicity of combining S-1 or S-1 plus cisplatin with intensity modulated radiation therapy for esophageal squamous cell carcinoma.

## Objectives

2

### Primary

2.1

The primary outcome is the rate of complete response.

### Secondary

2.2

The secondary outcomes are the overall survival rate, progression-free survival rate, toxicity.

## Methods/design

3

### Recruitment and study design

3.1

This trial is a prospective, randomized, multicenter phase II clinical trial. Patients with unresectable or medically unfit for surgery and no distant metastasis of esophageal squamous cell carcinoma will be randomized into 2 groups (Fig. 1): one group receiving S-1 concurrent intensity-modulated radiotherapy treatment (experimental group) and S-1 plus cisplatin concurrent intensity modulated radiation therapy (control group).

**Figure 1 F1:**
[figure not shown]
The plan of the clinical trial.

Before the start of treatment, the recruitment of eligible participants firstly includes the explanation, to each potential study participant, of the common ethical issues, purpose, design, description of the 2 different chemotherapy regimens, implementation, requirements, timeline of this study.

#### Inclusion criteria

3.1.1

1.Histology or cytology confirmed esophageal squamous cell carcinoma.2.There are measurable lesions according to the Response Evaluation Criteria in Solid Tumors (RECIST) standard.3.Patients with technically unresectable cancer or those with surgical contraindications and those who refused to undergo surgery.4.Clinical stage I to III.5.Age 18 to 75.6.ECOG physical performance score 0 to 1.7.No esophageal perforation or active esophageal bleeding, no obvious trachea or thoracic major vascular invasion.8.Chest radiotherapy, chemotherapy, immunotherapy, or biological therapy has not been performed before.9.Hemoglobin is greater than 100 g/L, platelet over 100 × 10^9^/L, absolute neutrophil count over 1.5 × 10^9^/L.10.The serum bilirubin is less than or equal to 1.5 times the upper normal limit (UNL).11.AST (SGOT) and ALT (SGPT) are less than or equal to 2.5 times the UNL.12.Alkaline phosphatase is less than or equal to 5 times the UNL.13.Serum creatinine or creatinine clearance is less than or equal to 1.25 times the UNL.14.Without interstitial pneumonia or a history of interstitial pneumonia.15.Have signed a Declaration of Informed Consent.

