#### Exclusion criteria

3.1.2

1.A history of chest radiotherapy, chemotherapy, or surgical resection of EC.2.The primary lesions are multifocal EC.3.The distance between the gastroesophageal junction and the lower bound of the esophageal primary lesion is less than 3 cm.4.Severe cardiovascular or pulmonary disease, interstitial pneumonia or a history of interstitial pneumonia.5.Patients with distant metastases.6.There are obvious esophageal ulcers, moderate pain in the chest and back, or symptoms of esophageal perforation.7.Patient cannot understand the test requirements, or patients may not be able to comply with the requirements of the tests.8.There are other malignant lesions in the patient, not including curable skin cancer (non melanoma), cervical carcinoma in situ, or malignant disease cured ≥5 years prior.9.Known to have 3 to 4 levels of allergic reactions to the treatment.10.Participated in other clinical trials in the past 30 days.11.Patient's esophagus is completely blocked or cannot swallow the S-1.12.Patients have esophageal stent.13.The researchers believe that there is an obvious disease present, meaning that the patient should be excluded from this study.

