#### Drop-out criteria

3.1.3

Criteria that will lead to the drop-out of a patient before completion of this study may be any kind of treatment for medical reasons or impairment that will result in an interruption or early completion of treatment, include:

1.The withdrawal of the informed consent of patients.2.Patient safety events.3.Chemotherapy delays because of toxicity lasting for more than 2 weeks.4.The patient enrolled in another study during the clinical study.5.Patient does not want to continue to participate.6.The compliance of the patient is not sufficient.7.The researchers’ judgment.

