### Chemotherapy

3.3

The experimental group will receive chemotherapy S-1 70 mg/m^2^ weekly from Monday to Friday until radiotherapy completion, then 2 weeks after completion of radiotherapy, 2 cycles of adjuvant chemotherapy consisting of S-1 70 mg/m^2^ from 1 to 14 days will be administered, each cycle consisting of 21 days. The control group will receive chemotherapy S-1 70 mg/m^2^ for the first 14 and 22 to 35 days, plus cisplatin 25 mg/m^2^ for the first 3 and 22 to 24 days. Two weeks after the end of radiotherapy, 2 cycles of adjuvant chemotherapy consisting of cisplatin 25 mg/m^2^ for the first 3 days and S-1 70 mg/m^2^ from 1 to 14 days will be administered, each cycle consisting of 21 days.

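### Inclusion criterion 13 puts a ceiling of 1.25 x UNL on creatinine clearance, so every reduced clearance satisfies that limb

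*Protocol article*

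**What the plan says.** Section 3.1.1 (Inclusion criteria) sets the renal entry rule in item 13: "Serum creatinine or creatinine clearance is less than or equal to 1.25 times the UNL". Item 10 of the same list gives the meaning of the abbreviation: "The serum bilirubin is less than or equal to 1.5 times the upper normal limit (UNL". The renal rule is thus an upper bound, and it applies to either measure.

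The neighbouring laboratory items run in the expected direction. Item 9 sets floors where low values are the worse ones, for example "Hemoglobin is greater than 100 g/L". Items 10 to 12 set ceilings for bilirubin, transaminases and alkaline phosphatase, where high values are the worse ones.

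Section 3.1.2 (Exclusion criteria) names organ disease in item 4, "Severe cardiovascular or pulmonary disease, interstitial pneumonia or a history of interstitial pneumonia", which does not include renal disease. Item 13 of that list is a general discretionary clause: "The researchers believe that there is an obvious disease present, meaning that the patient should be excluded from this study".

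Under section 3.3 (Chemotherapy) both arms receive S-1. In the concurrent phase the control arm's S-1 is given "plus cisplatin 25 mg/m^2^ for the first 3 and 22 to 24 days". Cisplatin is given again in the control arm's two adjuvant cycles.

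**The concern.** Serum creatinine rises as renal function falls, so a ceiling screens out impairment. Creatinine clearance falls as renal function falls, so screening out impairment needs a floor. Item 13 gives clearance a ceiling. Two consequences follow from that reversal:

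- A site that screens by clearance has no working renal threshold, because the limb can reject only high values.
- On the literal 'or', a patient whose creatinine exceeds 1.25 x UNL can still meet item 13 through low clearance.

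What is at stake is patient safety at entry. Cisplatin is given to one arm and S-1 to both. The article's Introduction justifies the trial by the toxicity of two-drug chemoradiotherapy, and toxicity is a secondary endpoint. The renal entry rule should do its job in either form in which a site may apply it.

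**Working it through.** There is no sample-size or error-rate figure to reproduce. The check is on the direction of an inequality.

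**Inputs.** The rule is creatinine <= 1.25 x UNL or clearance <= 1.25 x UNL (section 3.1.1, item 13). UNL is the upper normal limit (item 10). The article gives no numerical UNL for clearance, so 100 to 140 mL/min is assumed for illustration only.

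**General argument, which needs no assumed figure.** Reduced clearance means a value below the lower normal limit. Then

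reduced clearance < lower normal limit < UNL < 1.25 x UNL.

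Every reduced clearance meets the limb, whatever the laboratory's normal range.

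**Illustration.** Ceiling = 1.25 x UNL:

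- UNL 100: 1.25 x 100 = 125 mL/min
- UNL 120: 1.25 x 120 = 150 mL/min
- UNL 140: 1.25 x 140 = 175 mL/min

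Clearances of 10, 30, 50, 80 and 120 mL/min are below all three ceilings and pass. A clearance of 180 mL/min is above all three and fails.

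**How the limbs combine.** The table tests item 13 alone, not overall eligibility. The results are the same at all three assumed UNLs.

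| Patient | 'or' (as written) | if read as 'and' | clearance only | creatinine only |
|---|---|---|---|---|
| A: creatinine 1.0 x UNL, clearance 30 mL/min | pass | pass | pass | pass |
| B: creatinine 3.0 x UNL, clearance 30 mL/min | pass | fail | pass | fail |
| C: creatinine 1.0 x UNL, clearance 180 mL/min | pass | fail | fail | pass |

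Patient B shows the effect of the reversal: the clearance limb admits a patient whom the creatinine limb alone would reject. Patient C shows the mirror image: where the clearance limb decides, it turns away a patient with high clearance and creatinine within the limit.

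Patient A is different. A passes in every column, including the one that uses creatinine alone. That result comes from the absence of a minimum clearance and not from the reversed sign.

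**Does anything else in the visible text correct it?** No minimum clearance is stated, and no exclusion names renal disease. Exclusion 13 is discretionary and sets no renal limit. The drop-out criteria in section 3.1.3 include "Chemotherapy delays because of toxicity lasting for more than 2 weeks", safety events and the investigator's own judgement. All of these act after enrolment.

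**The case against.** The strongest reply is that this is a wording slip in one line. All the neighbouring laboratory limits point the right way, the creatinine limit remains readable and correct, and sites may well use creatinine alone. Nothing shows that any site screens by clearance only, and admitting a patient with creatinine at 3.0 x UNL because clearance is low would be a perverse use of the rule. Investigator discretion before enrolment and the drop-out criteria afterwards give some protection. The article also condenses a full protocol that is not shown, and the operative wording there may be correct.

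Much of this stands, and it limits the point. It does not remove it. The article does not merely leave a detail to the full protocol; it states a threshold, and states it in the wrong direction. The intended direction can be guessed, but the intended minimum cannot be recovered from the text, so sites in a multicentre trial would each have to supply their own.

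Three stronger readings are tempting and are not supported:

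- A reader might infer that the reversal is what lets in patients with normal creatinine and low clearance. It is not. Such patients would also pass if the clearance limb were deleted; only a minimum clearance would stop them.
- A reader might infer that the article contains no renal floor at all. Figure 1 and Table 1 are not shown, so the statement covers the visible text only.
- A reader might infer that patients with renal impairment were enrolled or harmed. The document gives no information on that.

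**Conclusion.** The point holds as an error of direction in one eligibility item. The clearance limb of inclusion criterion 13 cannot reject reduced renal function, whatever the laboratory's normal range; the 100 to 140 mL/min range only illustrates this. Where a site uses clearance, item 13 gives no renal protection, and on the literal 'or' it can override the creatinine limit. Where a site applies the creatinine limit regardless of clearance, that limit works as intended.

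It should be fixed because it concerns safety at entry to treatment with S-1 in both arms and cisplatin in one. How much it matters in practice depends on how sites apply the item and on the wording of the full protocol, neither of which is visible. The number of patients affected cannot be derived. Nothing here bears on the sample size of 88, the significance level, the power or the validity of the randomised comparison.

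**What to change.** Keep the ceiling of 1.25 x UNL for serum creatinine. Replace the clearance limb with a minimum (>=), with the value set by the clinical team, and require both limbs to hold where clearance is measured. Patient B then fails on creatinine whatever minimum is chosen, patient A fails if the minimum is above 30 mL/min, and patient C passes with any minimum up to 180 mL/min.

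Deleting the clearance limb is a weaker alternative. It removes the reversed rule but does not screen out low clearance with normal creatinine. Leaving the two limbs as alternatives has the same weakness.

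Recruitment opened in October 2016 according to section 3.8, so patients already enrolled should be checked against the corrected wording. If the full protocol already states the rule correctly, only the article needs correcting.

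The cost is a one-line change to eligibility and a check of screening records. Some candidates may become ineligible; how many cannot be derived from the document.

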#### Exclusion criteria

3.1.2

1.A history of chest radiotherapy, chemotherapy, or surgical resection of EC.2.The primary lesions are multifocal EC.3.The distance between the gastroesophageal junction and the lower bound of the esophageal primary lesion is less than 3 cm.4.Severe cardiovascular or pulmonary disease, interstitial pneumonia or a history of interstitial pneumonia.5.Patients with distant metastases.6.There are obvious esophageal ulcers, moderate pain in the chest and back, or symptoms of esophageal perforation.7.Patient cannot understand the test requirements, or patients may not be able to comply with the requirements of the tests.8.There are other malignant lesions in the patient, not including curable skin cancer (non melanoma), cervical carcinoma in situ, or malignant disease cured ≥5 years prior.9.Known to have 3 to 4 levels of allergic reactions to the treatment.10.Participated in other clinical trials in the past 30 days.11.Patient's esophagus is completely blocked or cannot swallow the S-1.12.Patients have esophageal stent.13.The researchers believe that there is an obvious disease present, meaning that the patient should be excluded from this study.

#### Drop-out criteria

3.1.3

Criteria that will lead to the drop-out of a patient before completion of this study may be any kind of treatment for medical reasons or impairment that will result in an interruption or early completion of treatment, include:

1.The withdrawal of the informed consent of patients.2.Patient safety events.3.Chemotherapy delays because of toxicity lasting for more than 2 weeks.4.The patient enrolled in another study during the clinical study.5.Patient does not want to continue to participate.6.The compliance of the patient is not sufficient.7.The researchers’ judgment.

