### Assessment of the primary and secondary endpoints

3.5

In this trial, endoscopic complete response (CR) 3 months after completion of treatment will be evaluated as the primary endpoint. Endoscopic CR was defined as the complete disappearance of any tumor ulceration or stenosis with no new lesion (all endoscopic pictures and reports had to be available), observation of the entire esophagus as defined by Tahara et al,^[22]^ but also no CT-scan progression. Biopsies were not mandatory. Tumor responses were assessed during week 15 according to RECIST guidelines.^[23]^ The primary tumor was assessed on CT scan with measure of the vertical length and maximal thickness of the esophageal wall on transverse plane. Secondary endpoints are the toxicity, progression-free survival (PFS), and overall survival (OS). Adverse events will be encoded in accordance with the requirements of Med DRA. Severity of adverse events will be graded according to the NCI-CTC classification criteria. The toxicity of the treatment, including acute and chronic toxicity will continue to be evaluated during treatment and during follow-up (Table 1). Any serious adverse drug reactions will be reported promptly to the hospital ethics committee. An intent-to-treat analysis (on all randomized patients) was planned for all other end points. PFS was defined as the date from randomization to tumor progression or death. OS was measured from date of study entry to date of death.

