**Table 1 T1:**
[figure not shown]
Evaluation of the treatment process.

The following conditions will be recorded at the end of the treatment (every 3 months during year 1–2, every 6 months thereafter):

1.Survival2.Physical condition based on the ECOG performance status score3.A physical examination4.Vital signs5.Electrocardiogram6.A barium meal7.Esophageal endoscopic biopsy (at the first follow-up time, and then at least once a year)8.CT scan for tumor evaluation (at the first follow-up time, and then at least once every 6 months).

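### Section 3.1.3 does not separate stopping treatment from leaving the study, so a literal reading would allow toxicity-related loss of OS, PFS and late-toxicity data

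*Protocol article*

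**What the plan says.** Protocol article, section 3.1.3 (Drop-out criteria), opens with "Criteria that will lead to the drop-out of a patient before completion of this study", so the event it defines is at study level. Its lead-in describes the trigger at treatment level, as medical treatment or "impairment that will result in an interruption or early completion of treatment". Seven items follow:

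- Items 1 and 5 concern the patient's own wish: withdrawn consent, and not wanting to continue.
- Item 2 is safety events.
- Item 3 is "Chemotherapy delays because of toxicity lasting for more than 2 weeks".
- Item 4 is "The patient enrolled in another study during the clinical study".
- Items 6 and 7 are insufficient compliance and the researchers' judgment.

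Section 3.5 names toxicity, PFS and OS as secondary endpoints. After describing the primary endpoint it states: "An intent-to-treat analysis (on all randomized patients) was planned for all other end points". It also says of toxicity, "including acute and chronic toxicity will continue to be evaluated during treatment and during follow-up".

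The follow-up list after Table 1 begins "The following conditions will be recorded at the end of the treatment", puts survival first, and sets visits every 3 months in years 1 and 2 and every 6 months after that. It makes no exception and no provision for drop-outs.

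Section 3.6 names the Kaplan–Meier method and allows for 10% drop-out per group.

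**The concern.** One list does two jobs. Stopping protocol treatment and leaving the study are different events, and only the second should end data collection. A site that takes section 3.1.3 at its word could close the record of a patient whose chemotherapy was delayed for toxicity, or who joined another trial after progression. That patient's later survival, progression and chronic-toxicity data would then be missing.

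Such loss would be unlikely to be random or balanced. The Introduction and Discussion rest the trial on the view that two-drug chemoradiotherapy is harder to tolerate, so toxicity-driven drop-out should fall more on the S-1 plus cisplatin arm. Kaplan–Meier estimation assumes that censored patients share the future risk of those still followed, which is doubtful for patients who stop for toxicity or poor compliance. If their prognosis is worse, the arm with more drop-outs looks better than it is. Its late toxicity is also observed least in the patients who tolerated treatment worst. Both effects could push the survival comparison towards the equal efficacy that the Discussion expects.

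The point concerns follow-up for OS, PFS and late toxicity. It does not concern the denominator of the primary complete-response rate.

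**Working it through.** **The texts side by side.** Section 3.1.3 takes patients out of the study for treatment-level reasons. Section 3.5 analyses OS, PFS and toxicity on everyone randomized. The list after Table 1 follows survival without exception. The last two can be carried out for all patients only if drop-outs under 3.1.3 are still followed, and the protocol does not say that they are.

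**The plan's own figures.** With 88 patients randomized 1:1 there are 44 per arm. The 10% drop-out allowance is 0.10 × 88 = 8.8, about 9 patients. The fix leaves the sample size unchanged.

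**Size if follow-up stopped at drop-out.** These inputs are assumptions, not taken from the documents: exponential OS; median 24 months in patients who do not drop out; drop-outs censored at 3 months; hazard ratio HR of drop-outs to the others. Let d be the share dropping out.

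- True 2-year OS = (1 − d) × 0.5 + d × 0.5^HR.
- Large-sample Kaplan–Meier value = [(1 − d) × 2^(−3/24) + d × 2^(−HR × 3/24)] × 2^(−21/24). After month 3 only the patients who did not drop out contribute.
- For HR = 2 the constants are 2^(−0.125) = 0.9170, 2^(−0.25) = 0.8409 and 2^(−0.875) = 0.5453.

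*10% in each arm, HR 2.* True: 0.9 × 0.5 + 0.1 × 0.25 = 47.5%. Kaplan–Meier: (0.9 × 0.9170 + 0.1 × 0.8409) × 0.5453 = 49.6%. Each arm is overstated by 2.1 points, and the difference is unbiased.

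*40% in control v 15% on S-1, HR 2.* The results are:

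| Arm | True 2-year OS | Kaplan–Meier | Overstated by |
|---|---|---|---|
| Control, d = 0.40 | 40.0% | 48.3% | 8.3 points |
| S-1, d = 0.15 | 46.25% | 49.4% | 3.1 points |
| Difference | 6.25 points | 1.0 point | |

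Simulations with censoring spread over 0.7 to 3.4 months agree: 6.2 to 6.3 points shrink to 0.9 to 1.1.

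*Sensitivity, 40% v 15%.* The hidden part of the difference is the gap between the two arms' biases.

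- HR 1: 0 points.
- HR 1.5: 5.0 − 1.9 = 3.1 points.
- HR 2: 8.3 − 3.1 = 5.2 points.
- HR 2.5: 10.5 − 3.9 = 6.6 points.

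*Smaller imbalance, 20% v 5%, HR 2.* The biases are 4.2 and 1.0 points, so about 3 points are hidden.

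*Lost events.* With d = 0.40 and HR 2, true control deaths by 24 months are 44 × 0.60 = 26.4. Observed deaths are 26.4 × 0.5 = 13.2 among patients who stay, plus 17.6 × (1 − 0.8409) = 2.8 among drop-outs, 16.0 in all. With HR 1 there is no bias, but deaths still fall from 22.0 to 13.2 + 17.6 × (1 − 0.9170) = 14.7.

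**The case against.** The strongest reply is that the protocol never says data collection ends at drop-out, nor that survival time is censored there. The list after Table 1 schedules survival follow-up without exception, and a patient who ends treatment early has also reached the end of treatment. Section 3.5 can be read as governing these endpoints. Censoring rules commonly sit in the full protocol or the analysis plan, and section 3.4 refers to a final statistical plan.

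Much of this stands. A reader might infer that follow-up does end selectively, that the curves are informatively censored, or that the intent-to-treat analysis is impossible. The documents support none of these. They leave the matter open, and intent-to-treat works if drop-outs are followed.

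A reader might also take the Introduction's best completion figure, 38.5%, and assume 100 − 38.5 = 61.5% drop-out in the control arm. That figure comes from retrospective studies of radiotherapy with 5-FU/cisplatin, a different regimen. The only drop-out rate that the trial states for itself is 10% per group. Entry to another study is also less clearly tied to prognosis than toxicity is.

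Scale matters too. At 44 per arm the standard error of a 2-year OS difference is √(0.40 × 0.60/44 + 0.4625 × 0.5375/44) = 10.5 points, so a 5.2-point distortion is about half of one standard error.

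What does not stand is the claim that this is only omitted detail. Section 3.1.3 states a rule, words it at study level, and mixes treatment-level reasons with withdrawn consent. An analysis plan can decide how to treat data that exist, but it cannot recover follow-up that sites did not collect.

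**Conclusion.** The point holds as a badly fixed rule. Section 3.1.3 does not distinguish stopping treatment from leaving the study and, read literally, conflicts with the intent-to-treat statement and the follow-up schedule in section 3.5. It would allow toxicity-related loss of OS, PFS and late-toxicity data, probably more in the two-drug arm.

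The size is conditional on follow-up actually stopping, and on the assumed median, hazard ratio and drop-out shares. It ranges from no bias (equal prognosis, or drop-outs still followed), through about 2 points per arm with an unbiased difference (10% in each arm, HR 2), to a 6-point difference shrinking to about 1 (40% v 15%, HR 2).

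The endpoints affected are secondary, and the trial is sized on complete response. The change should be made because it is cheap and lost follow-up may be unrecoverable, but the primary analysis does not depend on it.

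**What to change.** Reconcile section 3.1.3 with section 3.5 and the follow-up list after Table 1 in one short amendment, leaving the clinical criteria as they are:

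- Items 2, 3, 4, 6 and 7 of section 3.1.3 do not end study follow-up.
- Items 1 and 5 end follow-up only if the patient withdraws consent to follow-up. Record the date and the scope of that withdrawal.
- All other randomized patients stay on the existing visit schedule for survival, progression and toxicity.
- OS and PFS are not censored at treatment stop or at entry to another study.

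The cost is the amendment text and some extra follow-up effort for each early stopper, at visits that the protocol already schedules. The sample size of 88 is unaffected.
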